### **2.2 Institutional Review Board/Independent Ethics Committee**

Before study initiation, the investigator must have written and dated approval/favorable opinion from the IRB/IEC for the protocol, consent form, subject recruitment materials (eg, advertisements), and any other written information to be provided to subjects. The investigator or BMS should also provide the IRB/IEC with a copy of the Investigator Brochure or product labeling information to be provided to subjects and any updates.

The investigator or BMS should provide the IRB/IEC with reports, updates and other information (eg, expedited safety reports, amendments, and administrative letters) according to regulatory requirements or institution procedures.

### **2.3 Informed Consent**

Investigators must ensure that subjects are clearly and fully informed about the purpose, potential risks, and other critical issues regarding clinical studies in which they volunteer to participate.

In situations where consent cannot be given to subjects, their legally acceptable representatives (as per country guidelines) are clearly and fully informed about the purpose, potential risks, and other critical issues regarding clinical studies in which the subject volunteers to participate.

BMS will provide the investigator with an appropriate (ie, Global or Local) sample informed consent form which will include all elements required by ICH, GCP and applicable regulatory requirements. The sample informed consent form will adhere to the ethical principles that have their origin in the Declaration of Helsinki.

Investigators must:

- 1) Provide a copy of the consent form and written information about the study in the language in which the subject is most proficient prior to clinical study participation. The language must be non-technical and easily understood
- 2) Allow time necessary for subject or subject's legally acceptable representative to inquire about the details of the study
- 3) Obtain an informed consent signed and personally dated by the subject or the subject's legally acceptable representative and by the person who conducted the informed consent discussion
- 4) Obtain the IRB/IEC's written approval/favorable opinion of the written informed consent form and any other information to be provided to the subjects, prior to the beginning of the study, and after any revisions are completed for new information
- 5) If informed consent is initially given by a subject's legally acceptable representative or legal guardian, and the subject subsequently becomes capable of making and communicating his or her informed consent during the study, consent must additionally be obtained from the subject
- 6) Revise the informed consent whenever important new information becomes available that is relevant to the subject's consent. The investigator, or a person designated by the investigator, should fully inform the subject or the subject's legally acceptable representative or legal guardian, of all pertinent aspects of the study and of any new information relevant to the subject's willingness to continue participation in the study. This communication should be documented

The confidentiality of records that could identify subjects must be protected, respecting the privacy and confidentiality rules applicable to regulatory requirements, the subjects' signed ICF and, in the US, the subjects' signed HIPAA Authorization.

The consent form must also include a statement that BMS and regulatory authorities have direct access to subject records.

Subjects unable to give their written consent (eg, stroke or subjects with or severe dementia) may only be enrolled in the study with the consent of a legally acceptable representative. The subject must also be informed about the nature of the study to the extent compatible with his or her understanding, and should this subject become capable, he or she should personally sign and date the consent form as soon as possible. The explicit wish of a subject who is unable to give his or her written consent, but who is capable of forming an opinion and assessing information to refuse participation in, or to be withdrawn from, the clinical study at any time should be considered by the investigator.

The rights, safety, and well-being of the study subjects are the most important considerations and should prevail over interests of science and society.

### **3 INVESTIGATIONAL PLAN**

#### **3.1 Study Design and Duration**

This is a randomized, active-controlled, double-blind clinical trial. Approximately 200 treatment-naïve HIV-1 infected subjects will be randomized 1:1:1:1 to one of four treatment arms (approximately 50 per arm) with the resulting drugs/doses as follows:

- Arm 1: BMS-955176 60 mg QD + TDF/FTC 300/200 mg QD, or
- Arm 2: BMS-955176 120 mg QD + TDF/FTC 300/200 mg QD, or
- Arm 3: BMS-955176 180 mg QD + TDF/FTC 300/200 mg QD, or
- Arm 4: EFV 600 mg QD + TDF/FTC 300/200 mg QD

Randomization will be stratified by HIV-1 Clade (AE versus Other). The number of subjects with HIV-1 Clade AE will be capped at a maximum of approximately 16 total, approximately 4 per treatment arm.

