#### 1.1.1 *Rationale to support study design*

This Phase 2b study seeks to build on preliminary data from the Phase 2a studies to accomplish the goal of studying the efficacy of three different, once-daily doses (60, 120, and 180 mg) of BMS-955176 when given in combination with TDF/FTC. By accomplishing this primary objective, this Phase 2b study will provide supportive data in the context of a therapeutic, safe, and tolerable dose of BMS-955176 for subsequent development.

The Phase 2b clinical trial design is in general agreement with guidance from both US and EU regulatory agencies. Specifically, approximately 200 HIV-1 infected treatment-naïve adults will be randomized 1:1:1:1 to one of four treatment arms and receive treatment with three fully active ARVs (see [Section 1.1.3](#), Rationale to support any drug combinations).

In a recent clinical trial approximately 95% of randomized subjects were noted to be infected with HIV-1 clades B, C, and AE. Based on in-vitro studies, BMS-955176 is expected to be active against a variety of HIV-1 clades albeit with EC50s approximately 2-3 fold less toward HIV-1 clade AE compared to clade B (see [Section 1.4.1](#)). However, since the Phase 2a study

AI468002 did not include any subjects infected with HIV-1 clade AE (see [Section 1.4.1.3](#)), this multinational Phase 2b study will cap the total number of HIV-1 clade AE infected subjects to approximately 8% ( $n \approx 16$  total, approximately 4 per treatment arm) and stratify randomization to ensure each treatment group has approximately the same number of clade AE infected subjects. The study will be double-blind until after the analysis of the primary endpoint (at Week 24).

The primary endpoint will be evaluated after all subjects reach Week 24. Subjects in Arm 4 will receive Efavirenz (EFV) in double-blind fashion until after the Week 24 primary endpoint has been analyzed. Based upon these results, an efficacious, safe, and tolerable dose of BMS-955176 will be chosen (see [Section 3.1](#)). Subjects in experimental arms 1-3 will subsequently be transitioned to the open-label continuation dose of BMS-955176 (see [Section 3.1](#)). TDF/FTC will be provided to all subjects in an open-label fashion. The study duration is expected to be 96 weeks in length to assess durability of response and longer term safety and tolerability.

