#### **4.4 Method of Assigning Subject Identification**

At the start of the screening period, the investigative staff will call the Assignment Center via an Interactive Voice Response System ([IVRS], or its web-based equivalent) designated by the sponsor to enroll the subject and to obtain a subject patient identification number (PID).

For subjects who meet the protocol eligibility criteria, the investigative staff will call the IVRS and subjects will start treatment. Subjects will be randomly assigned 1:1:1:1 to one of

4 treatment arms, and stratified by HIV-1 Clade (AE versus Other), as described in [Section 3](#) and as outlined in the AI468038 Study Schematic [Figure 3.1.7-1](#).

*Note:* All efforts should be made to limit the possibility of randomizing subjects that do not start treatment. If a subject is randomized but does not receive study medication, the BMS study team must be notified immediately.

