##### **8.4.2.1 Primary Efficacy Analyses**

The primary efficacy endpoint is the proportion of subjects with plasma HIV-1 RNA < 40 c/mL at the Week 24 snapshot. This endpoint is assessed with the FDA snapshot algorithm. The primary analysis will be based on a modified ITT (mITT) approach. A sensitivity analysis will be conducted using an observed values approach. The two approaches will be implemented as follows:

- Modified ITT: The numerator will be based on subjects with plasma HIV-1 RNA < 40 c/mL at Week 24. The denominator will be based on all treated subjects
- Observed values: Similar to the mITT approach, the numerator will be based on subjects with plasma HIV-1 RNA < 40 c/mL at Week 24. However, the denominator will be based on the treated subjects with plasma HIV-1 RNA at Week 24

Response rates will be tabulated by treatment arm with exact binomial 95% confidence intervals.

Subgroup summaries will be provided to examine the impact of baseline viral load and HIV-1 Clade AE (Clade AE versus Other) for both the mITT and the observed values approach. Other subgroup summaries may be provided to examine the impact of other important covariates such as CD4+ count, sex, geographic region, etc.

At Week 24, a Time to Loss of Virologic Response (TLOVR) analysis will be conducted as a sensitivity analysis that compliments the snapshot analysis. The following definition for virologic rebound will be used:

“For subjects that have been confirmed as having reached virologic suppression, by having two consecutive HIV-1 RNA readings below the assay limit of detection (40 copies/mL), virologic rebound is defined as confirmed HIV-1 RNA levels above the limit of detection. For levels above the limit of detection, confirmation consists of either two consecutive readings, or a single reading followed by loss to follow-up.”

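### Week 24 arm rates are compared crude and randomisation balances clade only, so a small, avoidable amount of baseline viral-load noise stays in the dose comparison (minor)

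*Protocol*

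**What the plan says.** Section 3.1 sets the size: "Approximately 200 treatment-naïve HIV-1 infected subjects will be randomized 1:1:1:1 to one of four treatment arms (approximately 50 per arm". It names one stratification factor, "Randomization will be stratified by HIV-1 Clade (AE versus Other", and limits that stratum: "The number of subjects with HIV-1 Clade AE will be capped at a maximum of approximately 16 total, approximately 4 per treatment arm". Section 4.4 gives the IVRS the same single factor. Section 1.1.1 explains the choice: clade AE virus is less susceptible in vitro and was absent from the Phase 2a study, so its numbers are limited and spread evenly over the arms.

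Section 8.4.2.1 tabulates unadjusted Week 24 response rates by arm with exact binomial intervals, then adds: "Subgroup summaries will be provided to examine the impact of baseline viral load and HIV-1 Clade AE (Clade AE versus Other". Viral load comes first in that list, and the covariates that follow are described as further important ones. Section 8.4.7 compares each BMS-955176 arm with the EFV arm by an unadjusted one-sided Fisher test at 0.01. Under Section 3.1.5 the Week 24 analysis leads to the Continuation Dose.

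Section 3.3.1 sets a lower entry limit of 1000 c/mL for HIV-1 RNA and no upper limit. Table 5.1-1 measures HIV-1 RNA at screening, so the value is available when the IVRS is called on Day 1.

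**The concern.** The endpoint is a fixed threshold of 40 c/mL. A subject entering at 1000 c/mL needs a fall of log10(1000/40) = 1.4 log10. One entering at 100,000 c/mL needs log10(100,000/40) = 3.4 log10. It is therefore reasonable to expect baseline viral load to predict response, and the plan treats it as important. Yet the design balances a factor that sets apart at most about 8% of subjects and leaves to chance one that varies in all of them.

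The trial is labelled an estimation study, but the arms are compared, both for futility and for choice of dose. Section 1.1.2 itself expects exposures at 120 mg and 180 mg to overlap, so true differences between those doses may be small. With 50 per arm, any noise that can be removed from the comparison cheaply is worth removing. The question is how much there is.

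**Working it through.** **Inputs.** From the protocol: 50 per arm, 200 in total (Section 3.1); expected response 80% (Section 8.1); clade AE at most 16/200 = 8.0%. Assumed, because the protocol gives no figure: share q of subjects with high viral load, 0.2 to 0.5; response gap g between low and high viral load, 10, 20 or 30 points, the same in every arm.

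**1. The plan's own figure.** The exact 95% interval for 40/50 is 66.3% to 90.0%, which matches the stated 66% to 90%.

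**2. Chance imbalance.** With 200 subjects split 50 per arm, the difference in high-viral-load share between two arms has SD = sqrt[2q(1-q)/50 × 200/199]. At q = 0.3 this is 9.2 points; over q = 0.2 to 0.5 it is about 8 to 10 points. By simulation, the share ranges by 20 points or more across the four arms in 8%, 16%, 21% and 23% of trials for q = 0.2, 0.3, 0.4 and 0.5.

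**3. Effect on a two-arm difference.** Total variance is 2 × 0.8 × 0.2/50 = 0.0064, so SE = 8.0 points. Let pL = 0.8 + qg and pH = pL - g. With viral load exactly balanced the variance is 2[(1-q)pL(1-pL) + q pH(1-pH)]/50. The fraction removed is q(1-q)g²/(0.8 × 0.2).

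Worked case, q = 0.3 and g = 0.20: pL = 0.86 and pH = 0.66. Fraction removed = 0.21 × 0.04/0.16 = 5.25%. SE = 8.0 × sqrt(0.9475) = 7.79 points, a fall of 2.7%.

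| Gap | Variance removed, q = 0.2-0.5 | SE if balanced (points) | Fall in SE |
|---|---|---|---|
| 10 points | 1.0-1.6% | 7.94-7.96 | 0.5-0.8% |
| 20 points | 4.0-6.3% | 7.75-7.84 | 2.0-3.2% |
| 30 points | 9.0-14.1% | 7.42-7.63 | 4.6-7.3% |

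**4. Effect on what the team would see** (simulation, q = 0.3, g = 0.20). Over four equally effective arms, the average range in observed response is 11.6 points with viral load left to chance and 11.3 with it balanced. The chance of ranking two doses wrongly when they truly differ by 5 points is 27.4% against 27.0%; for a 10-point difference it is 12.3% against 11.8%.

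**5. What standardising alone recovers.** The table is a ceiling, reached when allocation is balanced. Standardising after an allocation that ignored viral load costs approximately 2[(1-q)pH(1-pH) + q pL(1-pL)]/50² in variance. For q = 0.3:

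- Gap 10 points: 0.006316 + 0.000144 = 0.006460, SE 8.04. No gain.
- Gap 20 points: 0.006064 + 0.000155 = 0.006219, SE 7.89. A fall of 1.4%.
- Gap 30 points: 0.005644 + 0.000159 = 0.005803, SE 7.62. A fall of 4.8%.

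**The case against.** The case for leaving the design alone is strong on most points.

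- Randomisation already makes the comparisons unbiased, and the exact intervals allow for chance imbalance. This stands.
- Clade has a stated scientific reason and a cap to enforce. Being listed first for subgroup summaries does not oblige the sponsor to stratify on viral load. This stands.
- Imbalance would be visible: baseline HIV-1 RNA is tabulated by arm (Section 8.4.1), response is summarised by baseline viral load, and dose choice also weighs safety and tolerability. This stands in part. Subgroup tables show an imbalance but do not correct the rates being compared.
- Standardised estimates are often left to the SAP, which was not available here. If the SAP has them, the analysis part of this point falls away.
- A full second factor has a cost. At a 30% share the clade AE, high-viral-load cell would hold about 16 × 0.3 = 4.8 subjects over four arms, and incomplete blocks there could disturb the intended clade balance. This stands and shapes the fix.

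A reader might also infer something stronger: that imbalance adds error large enough to reorder the doses. At q = 0.3 and a 20-point gap, the average range in high-viral-load share is 13.3 points, and 13.3 × 0.20 = 2.7 points of spread in expected response. But that spread combines in quadrature with binomial noise that no stratification removes, so the observed range changes by 0.3 points, not 2.7.

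**Conclusion.** The point holds as a minor, optional improvement. Clade is the only balanced factor, the Week 24 rates compared are crude, and a covariate that the plan treats as important is available for every subject and not used. What is lost is a little precision, not validity. Over the assumed shares, exact balance would lower the SE of a two-arm difference by under 1% at a 10-point gap, 2-3% at 20 points and 5-7% at 30 points. The risk of misranking two doses moves by about half a percentage point or less in the case simulated.

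The documents do not support reading this as biased comparisons, as an error in stratifying by clade, or as a material threat to the dose decision. All sizes rest on a share and a response gap that the protocol does not supply. If viral load predicts response only weakly, there is practically nothing to gain.

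**What to change.** In Section 8.4.2.1, specify before the Week 24 unblinding that arm rates and between-arm differences, standardised to the overall distribution of baseline viral load and clade, are reported beside the crude rates and considered in the dose comparison. The viral-load cut should be fixed in the same text. Keeping clade AE as a single cell avoids empty cells. The crude rates with exact intervals stay as the primary presentation. The cost is one table row per arm, from data already collected.

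Optionally, if enrolment timing allows, add screening HIV-1 RNA at one sponsor-chosen cut as an IVRS factor within the non-AE stratum only. That gives three strata instead of two and leaves the clade AE balance intact. The cost is an IVRS setting. It should be paired with the standardised estimate, because the crude exact intervals and the Fisher test would not show the gain in precision.

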##### **3.1.1 Screening**

The screening period begins with the subject's signature on the informed consent form (ICF).

The subject is then enrolled via the Interactive Voice Response System IVRS (or its web-based equivalent) See [Section 4.4](#).

If the subject meets all eligibility criteria, the subject must be randomized within the 42 day screening period.

##### **3.1.2 Day 1/Baseline Visit**

On the Day 1 Visit, subjects will begin QD dosing with the blinded BMS-955176 or blinded EFV, each in combination with open-label TDF/FTC (see [Section 4.5.1](#) for Instructions for Dose Administration).

The combinations assigned per arm of containers of BMS-955176 active dose/placebo and EFV active dose/placebo will achieve the designated dose of BMS-955176 60, 120, or 180 mg or EFV 600 mg so that treatment arms cannot be discerned:

- Subjects in Arm 1 will receive containers that have:
  - BMS-955176 60 mg active dose
  - BMS-955176 placebo matching 120 mg
  - EFV placebo matching 600 mg
  - open-label container of TDF/FTC 300/200 mg
- Subjects in Arm 2 will receive containers that have:
  - BMS-955176 placebo matching 60 mg
  - BMS-955176 120 mg active dose

- EFV placebo matching 600 mg
- open-label container TDF/FTC 300/200 mg
- Subjects in Arm 3 will receive containers that have:
  - BMS-955176 60 mg active dose
  - BMS-955176 120 mg active dose
  - EFV placebo matching 600 mg
  - open-label container TDF/FTC 300/200 mg
- Subjects in Arm 4 will receive containers that have:
  - BMS-955176 placebo matching 60 mg
  - BMS-955176 placebo matching 120 mg
  - EFV 600 mg active dose
  - open-label container TDF/FTC 300/200 mg

### **3.1.3      *Optional Week 2 Intensive PK Visit***

Subjects with anemia, defined as Hemoglobin < 11.0 g/dL, should be excluded from participation in the Week 2 Intensive PK Substudy.

Subjects in all arms will have the opportunity to participate in an elective Intensive PK Substudy visit at Week 2 (window for visit: Day 12-16). Approximately 48 subjects, 12 subjects from each arm, are expected to participate in the substudy; BMS may allow the substudy to over-enroll in an effort to have a sufficient number of complete datasets.

The series of 12 blood draws begins with pre-dose (0-hour) blood samples to be collected approximately 24 hours (20-28 hrs) after the morning doses of BMS-955176/placebo + TDF/FTC that were taken the day before. Ten more blood samplings are drawn through the 12-hr time point, with one final sampling collected at the 24-hr time point, requiring the subject to either remain overnight in the clinic, or to return the next morning; the final 24-hr sample will be collected prior to administration of the morning dose of BMS-955176/placebo + TDF/FTC (See [Section 5.5.1](#)).

PK Tools/Job Aids will be provided to assist with the proper sequencing of dosing and blood sample collections, as well as the collection of required data.

### **3.1.4      *Visits Week 4 - 96***

Subjects are expected to be treated for the duration of 96 weeks. After Day 1 and the optional Intensive PK visit at Week 2, subjects will be required to attend 12 more in-clinic study visits over the 96-week treatment period, as follows:

- Visits are conducted every 4 weeks from Week 4 through Week 16
- Visits are conducted every 8 weeks from Week 24 through Week 48
- Visits are conducted every 12 weeks from Week 60 through Week 96

Visits should be scheduled as an interval from the Day 1/Randomization date, and within a window of  $\pm 5$  days.

One of the visits should meet the very specific timing requirements as outlined in [Section 5.5.2](#) for a pre-AM dose blood collection.

Telephonic visit will be conducted with each subject at visit Weeks 20, 28, 36, 44, 54, 66, 78, and 90 to conduct an adherence assessment and to continue retention efforts.

### **3.1.5 Selection of the Continuation Dose, and the Switch to open-label study medications**

After the primary endpoint at Week 24 is reached (when all subjects have reached Week 24), BMS will conduct an analysis using the data through Week 24.

As described in [Section 8.4.7](#), an analysis of Virologic Futility will also occur. If a BMS-955176 dose arm meets criteria for Virologic Futility at Week 24, subjects in that arm will begin dosing with the next highest available remaining dose of BMS-955176.

Based upon the Week 24 analysis, a recommended dose for continuation will be selected\* and subjects in the BMS-955176 treatment arms will be unblinded and transitioned to the recommended, open-label Continuation Dose of BMS-955176; subjects in the EFV arm will be unblinded and transitioned to open-label EFV.

The open-label TDF/FTC backbone will remain unaltered.

*\* If the Continuation Dose cannot be clearly identified using the Week 24 data, the study will continue to be blinded to Investigator and subjects until an analysis of the Week 48 data can be performed and the Continuation Dose is selected.*

After the Continuation Dose is selected and once all of the logistics (eg, distribution of clinical drug supplies, activation of the new portion of the IVRS) have been completed globally, the transition of the subjects on the BMS-955176 arms to the open-label Continuation Dose, and of the subjects on the EFV arm to open-label EFV, will occur. It is anticipated that this transition will occur on or after all subjects have reached Week 48 (the earliest subjects to begin study treatment could be well beyond Week 48 when the switch to the open-label BMS-955176 or EFV occurs).

Investigators and subjects will be blinded to the treatment arm assignment (and to the dose of BMS-955176 for Arms 1-3) until after the switch to the Continuation Dose.

